## Abstract

**Background:**

Nutritional support is an essential part of the management of critically ill patients. However, optimal caloric intake has not been systematically evaluated. We aim to compare two strategies of enteral feeding: permissive underfeeding versus target feeding.

**Method/Design:**

This is an international multi-center randomized controlled trial in critically ill medical- surgical adult patients. Using a centralized allocation, 862 patients will be randomized to permissive underfeeding or target feeding. Patients in the permissive group receive 50% (acceptable range is 40% to 60%) of the calculated caloric requirement, while those in the targeted group receive 100% (acceptable range 70% to 100%) of the calculated caloric requirement. The primary outcome is 90-day all-cause mortality. Secondary outcomes include ICU and hospital mortality, 28-day, and 180-day mortality as well as health care-associated infections, organ failure, and length of stay in the ICU and hospital. The trial has 80% power to detect an 8% absolute reduction in 90-day mortality assuming a baseline risk of death of 25% at an alpha level of 0.05.

**Discussion:**

Patient recruitment started in November 2009 and is currently active in five centers. The Data Monitoring Committee advised continuation of the trial after the first interim analysis. The study is expected to finish by November 2013.

**Trial registration:**

Current Controlled Trials ISRCTN68144998

## Background

Nutritional support is an essential part of the management of critically ill patients
[1]. Although clinical trials have resolved the ‘when to start feeding’ question
[1], which is within 24 to 48 hours after admission to the ICU, there is little evidence to answer the ‘how much’ question. During critical illness, the metabolic rate is increased and complex fuel alterations occur. Fuel choice is altered from predominantly fat to glucose oxidation, thus glycolysis increases enormously. Proteolysis and lipolysis are also augmented
[2]. In a healthy person, exogenously supplied calories from fat or carbohydrate will suppress lipolysis and proteolysis
[2]. However, this suppression is blunted by acute inflammatory illness
[2]. In fact, excess caloric provision is increasingly perceived as having detrimental effects, particularly on mitochondria
[3], since it leads to increased oxygen radical production in addition to wasting fuel
[3].

In 1997, a review concluded that there was insufficient data from methodologically sound studies to permit firm recommendations about the optimal amount of nutritional support for critically ill patients
[4]. Likewise, the 2003 Canadian clinical practice guidelines concluded that whereas early enteral nutrition was recommended in critically ill patients, there were insufficient data to make recommendations on the dose of enteral feeding except for head-injured patients
[5]. Even in head injury patients, the recommendations for optimizing delivery of nutrients were based on only one randomized controlled trial(RCT)
[5].

The optimal caloric intake in the critically ill remains controversial. This controversy has been heightened with recent evidence suggesting harm and other studies suggesting benefit with the use of lower caloric intake in the critically ill. In a single-center RCT of 82 head-injured patients, the effect of ‘early-enhanced’ enteral nutrition (59.2% of caloric goal) was compared with standard nutrition (36.8% of caloric goal). At three months, the enhanced nutrition group had a trend towards better neurological outcome in comparison to the standard nutrition group and fewer overall complications, including infections
[6]. However, there were no differences in neurological outcome at six months or in mortality
[6]. The multicenter cluster-randomized Algorithms for Critical Care Enteral and Parenteral Therapy (ACCEPT) trial investigated the impact of implementing evidence-based feeding algorithms on nutrition practices and patient outcomes in the ICU
[7]. Patients in the intervention group received more calories per day than those in the control group (1,264 kcal versus 998 kcal, *P* = 0.31) and had a significantly shorter hospital length of stay (LOS) with a trend towards reduced mortality. Rubinson *et al.* showed that very low caloric intake (<25% of the average daily recommended calories) was associated with an increased risk of health care-associated bloodstream infections
[8]. A single-center RCT of 28 patients showed that lower energy deficits were associated with a decreased need for renal replacement therapy
[9].

There is also evidence to support outcome benefit with lower than standard targeted feeding goals. In a cohort study, Krishnan *et al.* found that moderate caloric intake (33% to 65% of the recommended American College of Chest Physicians (ACCP) targets) was associated with better clinical outcomes including reduced mechanical ventilation duration, ICU LOS, as well as hospital mortality, when compared with higher caloric intake
[10]. However, this study did not adjust for glucose control that has been found to influence outcomes in ICU patients. Dickerson *et al.* studied 40 critically ill, obese patients and found that patients who received fewer calories (<20 kcal/kg versus ≥20 kcal/kg) had decreased ICU LOS (*P* <0.03), reduced duration of antibiotic therapy (*P* <0.03), and a trend towards decreased mechanical ventilation duration (*P* = 0.09)
[11]. In a single-center quasi-RCT, 150 mechanically ventilated medical patients were administered ‘early aggressive’ feeding or ‘late’ feeding
[12]. The late group received fewer calories (629 ± 575 kcal versus 2,370 ± 2,000 kcal, *P* <0.001) and had a lower incidence of ventilator-associated pneumonia (30.7% versus 49.3%, *P* = 0.02), less *Clostridium difficile* induced diarrhea (4.0% versus 13.3%, *P* = 0.04), as well as shorter ICU LOS (9.8 ± 7.4 versus13.6 ± 14.2 days, *P* = 0.04) and hospital LOS (16.7 ±12.5 days versus 22.9 ± 19.7 days, *P* = 0.02) compared with the early feeding group
[12]. An RCT with 200 mechanically ventilated patients and a second RCT with 1,000 patients with acute lung injury showed that a strategy of initial trophic enteral feeding (10 mL/hour) compared with standard targeted enteral feeding goals for up to six days reduced gastrointestinal tolerance, but did not improve ventilator-free days or 60-day mortality
[13,14]. The intervention arms of these two RCTs instituted very low trophic feeding in critically ill patients with acute lung injury. In contrast, an RCT of 240 general medical-surgical mechanically ventilated patients conducted by our investigative team compared the efficacy of a moderate hypo caloric (60% to 70% of calculated caloric requirement) versus a eucaloric (90% to 100%) diet
[15]. The endpoints of ICU, 28-day and 90-day mortality were not statistically different (17.5%, versus 21.7%, *P* = 0.42; 18.3% versus 23.3%, *P* = 0.34 and 31.0% versus 39.3%, *P* = 0.19, respectively)
[15]. However, hospital mortality was reduced in the hypo caloric diet group (30% versus 42.5%, *P* = 0.04), and there was a trend towards shorter ICU LOS
[15]. In contrast to very low caloric or trophic enteral feeding, it remains unclear whether a moderate caloric intake may improve survival and reduce morbidity.

### Rationale for the study

There is a lack of conclusive evidence regarding the caloric intake dose required for enteral feeding in critically ill patients. The available literature reports mainly on observational studies that do not provide the best evidence and existing RCTs are either conducted on specific patient populations or are not conclusive. The objective of our Permissive Underfeeding versus Target Enteral Feeding in Adult Critically Ill Patients (PermiT) trial is to assess the effect of permissive underfeeding versus target feeding on 90-day mortality in adult, medical-surgical critically ill patients.

## Methods/design

### Study population, inclusion and exclusion criteria

All patients admitted to the participating ICUs are screened daily for study eligibility. Patients are deemed eligible for this study if they are ≥18-year old, receiving enteral feeding, and expected to remain in ICU ≥72 hours (Time Zero would be the time of ICU admission). Exclusion criteria are: lack of commitment to ongoing life support, brain death, pre-existing condition with expected six month mortality >50%, enteral feeding not started within 48 hours of ICU admission, parenteral nutrition (PN), oral feeding, previous enrollment in this study within the same hospital admission, pregnancy, post liver transplantation, post cardiac arrest, burns, prisoners, and receipt of vasopressors (except dobutamine) at the following doses: norepinephrine >0.4 μg/kg/min, epinephrine >0.4 μg/kg/min, dopamine >20 μg/kg/min, phenylephrine >300 μg/min, vasopressin >0.04 unit/min or half of these doses for patients receiving two or more vasopressors. Patients who are initially ineligible are reassessed multiple times for eligibility within the randomization window of 48 hours.

Eligible patients are not randomized (eligible non-randomized) if their substitute decision makers decline consent, the research team is unable to get consent within 48 hours of eligibility, the treating ICU physician does not agree with the patient being enrolled in the study or if the patient is already enrolled in a trial of a similar nature or outcome.

### Randomization

PermiT is a multicenter open-label international RCT. The patients who meet all inclusion with no exclusion criteria are randomized into one of the two intervention arms: the permissive underfeeding group or target feeding group. Randomization is based on computer-generated random permuted blocks of four and is stratified by center and follows a concealed process using sealed and numbered envelopes that allocate the patient to either of the two arms of the study.

Patients may be randomized into PermiT only once unless they were discharged from the hospital and were re-admitted beyond 180 days of the first enrollment. The study does not allow cross-overs and if any occur, they will be reported as protocol violations.

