### Analytical plan

#### Sample size

In our recent RCT
[15], we observed an absolute risk reduction in hospital mortality of 8% (95% CI 0.4% to 25%). Based on an estimated 90-day mortality of 25% and using a power of 80% and an alpha of 0.05, the sample required to demonstrate a decrease in mortality of 8% was 431 in each group (a total of 862 patients). The flow of patients through the study will be displayed in a ‘CONSORT’ diagram (Figure
1). 

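### A single fixed block size of four, stratified only by center and published during recruitment, makes part of the allocation sequence of this open-label trial predictable to site staff

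*Protocol article*

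**What the plan says.** The Randomization section gives one block size, one stratification factor and the means of concealment: "Randomization is based on computer-generated random permuted blocks of four and is stratified by center and follows a concealed process using sealed and numbered envelopes". The same section states that "PermiT is a multicenter open-label international RCT".

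The abstract (Method/Design) describes the mechanism differently: "Using a centralized allocation, 862 patients will be randomized to permissive underfeeding or target feeding". The article does not say who holds or opens the envelopes.

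Two further statements bear on the point:

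- Under Study population, inclusion and exclusion criteria, an eligible patient is not randomized if "the treating ICU physician does not agree with the patient being enrolled in the study". Consent must also be obtained within 48 hours of eligibility.
- The abstract (Discussion) says: "Patient recruitment started in November 2009 and is currently active in five centers". The block size was therefore made public before recruitment ended.

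**The concern.** An envelope hides its own content. It does not hide what earlier allocations in the same block already reveal. With every block equal to four and one sequence per center, the fourth allocation follows from the first three, and the third follows from the first two whenever those match.

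Past allocations are visible at the bedside. The arms differ openly in caloric target (Trial interventions), and the permissive arm receives extra saline or water every four hours (Other co-interventions).

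The step before randomization includes clinical discretion. A physician with a view on which strategy suits a particular patient could decline enrolment when the next allocation is known. The arms would then differ in baseline risk from the start. Analyzing patients as randomized does not repair that, because the distortion lies in who was randomized. An objective endpoint does not repair it either, because deaths would be counted correctly in groups that are not comparable.

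**Working it through.** **Inputs.** Block size 4, stratification by center only, open-label (Randomization). Allocation 1:1, with 431 per group and 862 in total (Sample size). At the first interim analysis in March 2012, 287 patients had completed the 90-day outcome (Discussion and Trial status).

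**The plan's own figure.** The article gives no predictability figure. Its sample size reproduces: 25% versus 17%, 80% power and two-sided 5% give 406 per group without continuity correction and 431 with it. This confirms two equal arms and plays no further part.

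**Certain allocations in a block of four.** There are six equally likely sequences with two A and two B.

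- AABB and BBAA: positions 3 and 4 are certain, so 2 each.
- ABAB, ABBA, BAAB and BABA: only position 4 is certain, so 1 each.
- Expected number per block = (2×2 + 4×1)/6 = 1.333.
- Share = 1.333/4 = 33.3%.

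**Best-guess accuracy, by position.**

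- Position 1: 1/2.
- Position 2: 2/3, because two of the three remaining places belong to the other arm.
- Position 3: 1/3 × 1 + 2/3 × 1/2 = 2/3.
- Position 4: 1.
- Mean = (1/2 + 2/3 + 2/3 + 1)/4 = 70.8%, against 50% under simple randomization.

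**Other block sizes, by the same enumeration.**

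| Blocks | Expected certain per block | Certain share | Best-guess accuracy |
|---|---|---|---|
| 4 | 1.333 | 33.3% | 70.8% |
| 6 | 1.5 | 25.0% | 68.3% |
| 8 | 1.6 | 20.0% | 66.6% |
| 4, 6 and 8, equally frequent, each size known to staff | (1.333 + 1.5 + 1.6)/3 | 4.433/18 = 24.6% | 68.1% |

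The last row is an upper bound for a varying scheme. If staff do not know the size of the current block, they can rarely be certain where it ends.

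**Patients who could still be affected.** At most 862 − 287 = 575 patients lie beyond the first interim cohort, and 575/3 ≈ 192. This is a ceiling. The 287 are patients with a completed 90-day outcome, so others were already enrolled in March 2012, and more may have been enrolled before publication.

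**Scale of a possible effect (assumption, not from the document).** Suppose selection made baseline mortality risk differ between arms by 5 to 10 percentage points among the certain third. The overall difference would then shift by 5/3 to 10/3, or about 1.7 to 3.3 points, against the planned difference of 8 points. This supposes that all certain allocations at all centers were acted on. With only some of them acted on, the shift shrinks in proportion.

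**The case against.** The strongest reply is that predictability is not bias. The one-in-three rate holds only for someone who knows the block size, follows the center's sequence in order and can influence enrolment. The article does not say that sites were told the block size before publication. This stands, and it limits the claim to a vulnerability.

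A reader might infer that 862/3 ≈ 287 patients had foreseeable allocations over the whole trial. That would require sites to have known the block size since November 2009, which the document does not support. The agreement with the 287 patients of the interim analysis is a coincidence, since both are one third of 862.

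A reader might also infer that the abstract and the Methods contradict each other. They do not strictly do so, because envelopes can be prepared, held or opened centrally. A condensed article may leave custody to the full protocol. What stands is that the two descriptions differ and should be aligned. Central custody would not remove the predictability of fixed blocks of four within center.

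There are also safeguards. All admissions are screened daily, and consent is limited to 48 hours. A log of why eligible patients were not randomized goes to the coordinating center every three months (Informed consent). An independent monitor has access to source documents (Administrative and ethical aspects), and site visits review the consent process (Monitoring for safety). These can help to detect selective enrolment. They do not make the next allocation less predictable.

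Finally, varying block sizes reduces predictability without abolishing it. That is true, and the gain is largest when the sizes stay undisclosed.

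**Conclusion.** The point holds as a design weakness that should be corrected for the remaining patients. With fixed blocks of four within center, an expected 33.3% of allocations are certain and 70.8% can be guessed correctly by staff who know the block size and their center's earlier allocations. Open-label feeding, a single stratification factor and publication during recruitment make both conditions attainable. The physician's right to decline enrolment gives that knowledge a route to act.

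The conclusion does not go further. The document gives no evidence that any site predicted allocations or selected patients. It also does not allow a count of those still exposed, beyond the ceiling of about 190 certain allocations among at most 575 patients. The two descriptions of the allocation mechanism are unreconciled rather than incompatible. The sample size and the planned analyses are unaffected.

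**What to change.** For patients still to be randomized:

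1. Replace the lists with randomly varying block sizes within center, for example 4, 6 and 8, and do not disclose the sizes to sites or in publications until recruitment ends.
2. Release each allocation only after the patient has been irrevocably registered.
3. Make the abstract and the Randomization section describe the same method, including who holds the envelopes and who opens them.

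As an optional diagnostic for patients already enrolled, compare baseline APACHE II, which is already collected, by arm and by whether the allocation was predictable from its place in the block. This would show only selection related to severity, and a null result would not be proof of absence.

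The cost is new lists and a short amendment. The largest possible within-center imbalance rises from 2 to 4 patients, because an incomplete block of eight can be four apart. In return, the certain share falls from 33.3% to at most 24.6%, and lower while the sizes remain undisclosed.

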### Informed consent

The research coordinator and/or physician investigator explains the objectives of this study and its potential risks and benefits to the patient when possible or more commonly to his/her surrogate decision maker. Once the patient or his/her surrogate decision maker agrees, a witnessed written consent is obtained. The patient or surrogate can withdraw from the study at any time without impact on treatment. A screening log indicating why eligible patients were not randomized is recorded at each of the participating centers and reported back to the coordinating center on a three-month basis.

### Trial interventions and nutrition related co-interventions

Patients in the permissive underfeeding group receive 50% of the calculated caloric requirement (with an acceptable range of 40% to 60%) and those in the target feeding group receive100% of the calculated caloric requirement (with an acceptable range of 70% to 100%). These targets were selected to maintain moderate caloric intake in the permissive underfeeding group yet to achieve a larger separation in caloric intake between the two groups compared to our previous trial
[15]. Participating centers may use their own standard feeding protocols to achieve the caloric intake for both arms of the study. The coordinating center uses a feeding protocol that has been published earlier
[16]. Head of bed elevation, minimizing discontinuation of enteral feeding during diagnostic tests, nursing care or routine bedside procedures are followed according to the most current Society of Critical Care Medicine (SCCM) and American Society for Parenteral and Enteral Nutrition (ASPEN) clinical practice guidelines
[17]. After radiographic confirmation of tube placement (gastric or post-pyloric), feeding is started at 30 ml/hour and advanced by 10 ml/hour every four hours. To achieve the prescribed enteral feeding, daily targets are used in addition to the hourly rate
[18]. The protocol does not provide recommendations for the type of feeding tube (large-bore or small-bore nasogastric tube with or without guide wire). For patients fed with gastric tubes, the residuals are checked every four hours, and for post-pyloric tubes only if there are signs of feeding intolerance such as vomiting, abdominal distention or ileus. For small size tubes that do not permit aspiration, a second larger size tube may be placed into the stomach to aspirate the gastric residual. The protocol provides instructions on the management of residuals greater than 200 ml. Prokinetic agents and post-pyloric tubes for feeding intolerance are used at the discretion of the treating physicians. The decision to introduce PN is also at the discretion of the treating team. Our PermiT study recommends following the SCCM/ASPEN clinical practice guidelines, which considers PN for both the targeted and permissive underfeeding groups if caloric requirements are not met after 7 to 10 days by enteral route alone
[17].

#### Enteral formulations

The type of enteral formulations used is not directed by the study protocol and is left to the combined decision of the treating physician and the clinical dietitian as long as caloric targets are met. The types of formulae are classified into non-specialized (Ensure, Ensure Plus, Jevity (1.0 to 1.2), Osmolite, Resourse and Resourse Plus (from Nestle, Novartis and Abbott, Laboratories,) or specialized (Nepro, Pulmocare, Renal Nova Source, Glucerna, Nutren Hepatic, Suplena, Vivonex Plus and Peptamen (1.0, 1.2, and 1.5), and Promote (from Nestle, Novartis and Abbott Laboratories)). Beneprotein formula (from Novartis) is used to supplement protein. The choice of using either immune-modulating or non-immune modulating formulations is left to the discretion of participating centers. Suggestions on selection of enteral formulations depending on patients’ health status are outlined in Table
1 and consistent with the SCCM/ASPEN clinical practice guidelines
[17]. 

**Table 1 T1:** Guidelines for selection of enteral feeding formulation

**Diagnostic category**	**Enteral feeding formulation**
Major elective surgery, trauma, burns, headand neck cancer, and critically ill patients on mechanical ventilation (being cautious in patients with severe sepsis)	Immune-modulating enteral formulations (arginine, glutamine, nucleic acid, omega-3 fatty acids, and antioxidants). Grade A (surgical) Grade B (medical).
Acute lung injury/acute respiratory distress syndrome	Enteral formulation characterized by an anti-inflammatory lipid profile (that is, omega-3 fish oils, borage oil) and antioxidants (grade A).
All critically ill patients receiving specialized nutrition therapy	Antioxidant vitamins (including vitamins E and ascorbic acid) and trace minerals (specifically including selenium, zinc and copper).
Burn, trauma, and mixed ICU patients	Enteral glutamine to an enteral nutrition regimen.
Pulmonary failure	High-lipid low carbohydrate formulations are not recommended. Fluid-restricted calorically dense formulations should be considered.
Renal failure	Standard enteral formulations and standard ICU recommendations for protein and calorie.

